**6. AGENT FORMULATION AND PROCUREMENT**

**6.1 Study Agent**

# BAY 43-9006 tosylate (NSC 724772)

**Chemical Name:** 4–{4-[3-(4-chloro-3-trifluoromethyl-phenyl) ureido]-phenoxy}-pyridine-2 carboxylic acid methylamide-4-methylbenzensulfonate.

**Other Names:** BAY 54-9085 is the tosylate salt of BAY 43-9006; sorafenib

**Classification:** Kinase inhibitor (Raf, VEGF-R, and PDGF-R)

**Mechanism of Action:**The ras/raf signaling pathway is an important mediator of responses to growth signals and angiogenic factors. This pathway is often aberrantly activated in human tumors due to presence of activated ras, mutant b-raf, or over expression of growth factor receptors.

BAY 43-9006 is a potent inhibitor of c-raf, and wild-type and mutant b-raf in vitro. Additionally, further characterization of BAY 43-9006 tosylate revealed that this agent inhibits several receptor tyrosine kinases (RTKs) that are involved in tumor progression (VEGF-R, PDGF-R, Flt3, and c-KIT) and p38α, a member of the MAPK family.

**Molecular Formula:** C12H16CIF3N4O3 X C7H8O3S

**M.W.:** BAY 43-9006 tosylate:637 Daltons; BAY 43-9006 (free base): 465 Daltons

**Approximate Solubility:** 0.19 mg/100 mL in 0.1 N HCl, 453 mg/100 mL in Ethanol, and 2971 mg/100 mL in PEG 400.

**How Supplied:** BAY 43-9006 tosylate is supplied as an immediate-release film-coated, round, and salmon color tablet containing 200 mg of the free base, BAY 43-9006, and the excipients croscarmellose sodium, microcrystalline cellulose, hydroxypropylmethylcellulose, sodium lauryl sulfate, and magnesium stearate. The film-coat consists of hydroxypropylmethyl cellulose, polyethylene glycol, tiranium dioxide and red iron oxide. The film coating has no effect on the rate of release of the active BAY 43-9006 tosylate.

BAY 43-9006 tosylate 200 mg tablets are supplied in bottles of 140 tablets.

**Storage:** Store at controlled room temperature (15ºC – 25ºC). Storage conditions should not exceed 25ºC.

**Stability:** Stability studies with the 200 mg dosage form are ongoing. The current shelf life is 24 months when stored at controlled room temperature.

**Route**(s) **of Administration:** Orally

**Method of Administration:** BAY 43-9006 tosylate should be taken with at least 250 mL of water and can be given without regards to meals. Food does not appear to have a clear effect on BAY 43 9006 tosylate pharmacokinetics.

**Potential Drug Interactions:** BAY-9006 tosylate is metabolized by the P450 CYP3A enzyme and has been shown in preclinical studies to inhibit multiple CYP isoforms. Therefore, it is possible that BAY-9006 tosylate may interact with drugs that are metabolized by the P450 CYP isoenzymes or with drugs that inhibit CYP 3A. Close monitoring is recommended for patients taking agents with narrow therapeutic indices and metabolized by the liver, such as warfarin, phenytoin, quinidine, carbamazepine, phenobarbital, cyclosporine, and digoxin. Additionally, BAY-9006 tosylate is 97% to 99% protein bound; however, no drug interactions have been reported in studies, thus far.

**6.2 Agent Ordering**

Except in very unusual circumstances, each Participating Institution will order DCTD-supplied investigational agents directly from CTEP. Investigational agents may be ordered by a participating site only after the initial IRB approval for the site has been forwarded by the Coordinating Center to the CTEP PIO.

NCI-supplied agents may be requested by the Protocol Chair (or their authorized designees) at each Participating Institution. Pharmaceutical Management Branch (PMB) policy requires that the agent be shipped directly to the institution where the patient is to be treated. PMB does not permit the transfer of agents between institutions (unless prior approval from PMB is obtained). Completed Clinical Drug Requests (NIH-986) should be submitted to the PMB by [contact] or mailed to the Pharmaceutical Management Branch, CTEP, DCTD, NCI, [name].

**6.3 Agent Accountability**

The Investigator, or a responsible party designated by the investigator, must maintain a careful record of the inventory and disposition of all agents received from DCTD using the NCI Drug Accountability Record Form.

**7.0 CORRELATIVE/SPECIAL STUDIES**

**7.1** *BRAF* exon 15 and *NRAS* exon 3 will be sequenced from paraffin-embedded melanoma tumor tissues by the [name]/ [name] lab at NYU. In our published study, 92% of mutations in metastatic melanoma tissues were in BRAF exon 15. BRAF exon 11 will not be examined before treatment because our study indicated that only (2/77) 2.6% of metastatic melanoma tissues harbor this mutation. (Cancer Res. 2003 Jul 15;63(14):3955-7.) NRAS will be assessed despite its relatively rare occurrence (exon 3 mutations were found in only 4% of tumors in our study) because it functions upstream of BRAF. Activating mutations in NRAS, therefore, may lead to an increase in the level of BRAF activity and may explain why a patient with a wild-type BRAF tumor would response to treatment with BAY 43-9006.

We expect tumors from 6 or 7 patients to harbor a *BRAF* mutation and tumors from 1 or 2 patients to harbor an *NRAS* mutation. We anticipate that 2-3 patients will have no detectable mutation in either of these genes.

Representative tumor tissue sections will be sent to the [name]/[name] laboratory at NYU via hand delivery or overnight mail to ensure timely delivery. Genomic DNA will be extracted from paraffin tissue blocks using a Qiagen Tissue Kit (Qiagen, Valencia, CA). Exon 3 of N-RAS and exon 15 of BRAF will be amplified by PCR and sequenced using the methods described in our published paper. Turn-around time is expected to be within 10 days of receipt of tumor samples. (**Appendix C**)

**7.2** Tumor levels of CDK4, phospho-MAPK, and cyclin D1 will be assessed by our newly optimized quantitative immunohistochemistry. Expression of p85 PI3 kinase (expected to be unaffected by treatment) will be assessed as internal controls. (**Appendix D**).

These studies will be done using the formalin-fixed portion of the biopsies. By utilizing quantitative immunohistochemistry to determine relative alterations in protein expression levels, we eliminate the need for handling and delivery of frozen tissue. In addition, we will measure phosphorylated MAPK by immunohistochemistry using an antibody to the activated,phosphorylated MAPK (Cell Signaling Technology, Beverly,MA). These studies will be done using the formalin- fixed portion of the biopsies. As a result, these analyses will not exhaust tissues required for the immunoblotting studies described above.(**Appendix D**)

**7.3** We will use a fluorescent, mutant-specific PCR-based approach to detect circulating tumor cells that harbor the most common *BRAF* mutation (T1796A). For each patient, we will correlate our results with the presence of *BRAF* mutation in their tumor tissues, as well as their response to treatment (**See Appendix E**).

- 1. A variety of studies have suggested that cellular interactions with the Extracellular Matrix (ECM) can regulate a wide variety of cellular functions including adhesion, migration and proliferation (31). Angiogenesis, malignant tumor growth and metastasis all require proteolytic remodeling of components of extracellular matrix (32). Interestingly, three studies have suggested that cellular interactions with the Extracellular Matrix (ECM) can regulate a wide variety of cellular functions including adhesion, migration and proliferation (31). Angiogenesis, malignant tumor growth and metastasis all require proteolytic remodeling of components of extracellular matrix (32). Interestingly, recent studies have identified cryptic regulatory epitopes that are normally hidden within the three dimensional structure of the ECM protein collagen (33), (34). Under normal physiological conditions these cryptic epitopes of collagen are not exposed (33), (34). However, following proteolytic remodeling of the collagenous ECM during tumor growth and invasion these unique cryptic epitopes are exposed and can be recognized by two novel monoclonal antibodies termed HUIV26 and HUI77 (33), (34). The functional cryptic epitopes defined by these unique Mabs have been shown to be specifically associated with angiogenic blood vessels and proliferating tumors in vivo, while little if any was detected within normal tissues (33), (34). These findings suggest that exposure of these epitopes may correlate with induction of angiogenesis and tumor progression (33), (34). Interestingly, during collagen synthesis pro-peptide segments of the collagen chains are cleaved and released into the circulation as part of the collagen fibril formation. In fact, investigators have developed an ELISA based assay to quantify the levels of collagen pro-peptide and found a correlation with tumor growth and metastasis (35), (36). Based on these studies, the possibility that [name] laboratory’s unique cryptic epitopes of collagen could also be cleaved and released into the systemic circulation was tested. [name] and colleagues have developed an ELISA based assay to detect soluble HUIV26 and HUI77 cryptic epitopes that is based upon a sandwich assay employing the use of a biotinylated anti-type IV collagen polyclonal antibody along with an anti-biotin monoclonal antibody conjugated to horseradish peroxidase as depicted in Figure 7. This assay has been subjected to an extensive validation regimen and as shown in Figure 8 and has the necessary range of linearity and sensitivity to allow it to be amenable for the monitoring of a clinical protocol where serial samples will be monitored. Figure 9 also demonstrates the results of preliminary findings which indicate that the cryptic epitopes of collagen can be detected in serum from melanoma patients. Importantly, the levels of these cryptic epitopes were significantly elevated in serum from melanoma patients as compared to serum from normal subjects. These findings suggest the possibility that the levels of cryptic collagen epitopes may correlate with extent of tumor burden, invasion and metastasis. Thus, serum levels of these unique cryptic epitopes may be useful to monitor the course of diseases following therapeutic intervention. We will examine levels over the duration of treatment and will examine the relationship with the extent of tumor burden. (**Appendix F**)

[figure not shown]

# Figure 7. Key elements of ELISA assay to detect HUIV26 and HUI77 cryptic epitopes of collagen.

[figure not shown]

# Figure 8. Representative standard curves showing the linear range of the ELISA assay for the detection of HUIV26 and HUI77 collagen cryptic epitopes in human serum.

[figure not shown]

**Figure 9**. Scatter graph showing the cluster of denatured TYPE IV collagen cryptic epitope values in serum from melanoma patients compared to normal controls using HU177 antibody.

**8. STUDY CALENDAR**

Baseline evaluations are to be conducted no more than 1 week prior to administration of study agent. Scans and x-rays must be done no more than 4 weeks prior to the start of therapy. In the event that the patient’s condition is deteriorating, laboratory evaluations should be repeated no more than 48 hours prior to initiation of the next cycle of therapy.

|  | **Pre-Study (<14 days before starting drug)** | **Each cycle** | | | **Every 2 cycles** | **Off Study** |
| --- | --- | --- | --- | --- | --- | --- |
| **D1** | **D8*,15*,22*** | **D28** |
| BAY 43-9006 |  | X | X | X |  |  |
| **Informed consent** | X |  |  |  |  |  |
| **Demographics** | X |  |  |  |  |  |
| **Medical history** | X |  |  |  |  |  |
| **Physical exam** | X | X |  | X |  | X |
| **Vital signs** | X | X | X | X |  | X |
| **Height / Weight** | X | X |  |  |  | X |
| **Medications** | X | X |  |  |  | X |
| **Performance status** | X | X |  | X |  | X |
| **Hb, ANC, plts** | X | X |  |  |  | X |
| **Serum chemistry**** | X | X |  |  |  | X |
| **EKG** | X |  |  |  |  |  |
| **B-HCG** | X |  |  |  |  |  |
| **Adverse Events** |  | X |  |  |  | X |
| **Tumor Measurements** |  | X |  | X1 | X2 | X |
| **Collection of PBPC’s** |  | X |  | X |  | X |
| **Collagen Cryptic Epitopes** |  | X |  | X |  |  |
| **Tumor Biopsy** |  | X*** |  | X***† |  |  |
| **PT/INR if on therapeutic anti-coagulation** | X | X | X | X |  | X |

* Weekly blood pressures will be done for the first cycle.

**Electrolytes, calcium, magnesium, liver function tests (AST, ALT, total bili) and LDH.

*** Biopsies done only on Cycle 1.

† The post treatment tumor biopsy will be conducted 18-48 hours after the first treatment cycle.

1 Day 28 tumor measurements will be based on the measurement of tumors sites that can be assessed by clinical exam.

2 The every other cycle, day 28 tumor measurements will be assessed by imaging studies.

**9.0 MEASUREMENT OF EFFECT**

For the purposes of this study, patients should be reevaluated for response every 2 cycles. In addition to a baseline scan, confirmatory scans should also be obtained *not less than 4* weeks following initial documentation of objective response.

**9.1 Definitions**

Response and progression will be evaluated in this study using the new international criteria proposed by the Response Evaluation Criteria in Solid Tumors (RECIST) Committee [*JNCI* 92(3):205-216, 2000]. Changes in only the largest diameter (unidimensional measurement) of the tumor lesions are used in the RECIST criteria. Note: Lesions are either measurable or non-measurable using the criteria provided below.

**9.1.1 Measurable disease**

Measurable lesions are defined as those that can be accurately measured in at least one dimension (longest diameter to be recorded) as 20 mm with conventional techniques (PET, CT, MRI, x-ray) or as 10 mm with spiral CT scan. All tumor measurements must be recorded in millimeters.

**Note:** Tumor lesions that are situated in a previously irradiated area will be considered measurable only if there has been documented progression of the lesion since completion of radiotherapy.

Clinical lesions

Clinical lesions will only be considered measurable when they are superficial (e.g., skin nodules and palpable lymph nodes). In the case of skin lesions, documentation by color photography, including a ruler to estimate the size of the lesion, is recommended.

Chest x-ray

Lesions on chest x-ray are acceptable as measurable lesions when they are clearly defined and surrounded by aerated lung. However, CT is preferable.

Conventional CT and MRI

These techniques should be performed with cuts of 10 mm or less in slice thickness contiguously. Spiral CT should be performed using a 5 mm contiguous reconstruction algorithm. This applies to tumors of the chest, abdomen, and pelvis. Head and neck tumors and those of extremities usually require specific protocols.

Ultrasound (US)

When the primary endpoint of the study is objective response evaluation, US should not be used to measure tumor lesions. It is, however, a possible alternative to clinical measurements of superficial palpable lymph nodes, subcutaneous lesions, and thyroid nodules. US might also be useful to confirm the complete disappearance of superficial lesions usually assessed by clinical examination.

Endoscopy, Laparoscopy

The utilization of these techniques for objective tumor evaluation has not yet been fully and widely validated. Their uses in this specific context require sophisticated equipment and a high level of expertise that may only be available in some centers. Therefore, the utilization of such techniques for objective tumor response should be restricted to validation purposes in reference centers. However, such techniques may be useful to confirm complete pathological response when biopsies are obtained.

Cytology, Histology

These techniques can be used to differentiate between partial responses (PR) and complete responses (CR) in rare cases (e.g., residual lesions in tumor types, such as germ cell tumors, where known residual benign tumors can remain).

The cytological confirmation of the neoplastic origin of any effusion that appears or worsens during treatment when the measurable tumor has met criteria for response or stable disease is mandatory to differentiate between response or stable disease (an effusion may be a side effect of the treatment) and progressive disease.

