A phase 1 study is determining the MTD, DLT, PK, and pharmacodynamics in patients with advanced, refractory solid tumors (24). BAY 43-9006 was administered on a regimen of repeat cycles of 1 week on/1 week off using b.i.d. dosing. There were 19 evaluable patients (8 colorectal, 4 sarcoma, 2 pancreas, 1 renal cell carcinoma, 1 melanoma, 1 mesothelioma, 1 cervical, and 1 unknown primary) at 5 dose levels; 100 mg (3 pts), 200 mg (3 pts), 400 mg (4 pts), 600 mg (6 pts), and 800 mg (3 pts). Grade 3 and 4 adverse events of dyspnea, hypertension, hyponatremia, increased prothrombin time, and rash were reported. Rash was observed at all dose levels. Toxicities were rapidly reversible and no myelosuppression was seen. There were 5 drug-related DLTs (at 800 mg); 2 patients with grade 2 rash, 2 patients with grade 3 rash, and 1 patient with grade 3 hypertension. Five patients (cervical, renal, sarcoma, melanoma, and colon) had stable disease. The melanoma patient showed decreased 18[F]-fluorodeoxyglucose uptake on PET scan prior to progression of disease. The renal cell patient is still ongoing, with SD > 13 months. An increase in Cmax and AUC up to 400 mg BID was observed with increasing dose with a terminal half-life ranging from 16-53 hours. The MTD was established at 600 mg.

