**3. PATIENT SELECTION**

**3.1 Eligibility Criteria (Appendix A)**

3.1.1 Patients must have histologically or cytologically confirmedunresectable Stage III and Stage IV melanoma. The first 13 patients in each subgroup must have melanoma tumors amenable to biopsy before and after therapy and they must consent to having these biopsies done. These biopsies are necessary in order to carry out the correlative pharmacodynamic measurements (see below). In most cases, biopsied tumors will be cutaneous or subcutaneous metastases. If additional patients are accrued beyond the first 13- patients in each subgroup, we will obtain either real time biopsies or paraffin embedded tissue from a previous biopsy for prospective identification of the B-RAF mutation. This is necessary in order to subgroup patients. Since there has been a preponderance of wild type patients accrued to date, the protocol will allow enrollment to any patient with or without biopsy accessible metastatic disease in an attempt to expediciously complete the trial.

3.1.2 Patients must have measurable disease, defined as at least one lesion that can be accurately measured in at least one dimension (longest diameter to be recorded) as >20 mm with conventional techniques or as >10 mm with spiral CT scan. See section 9.1.1 for the evaluation of measurable disease.

3.1.3 No prior systemic chemotherapy for metastatic disease is permitted.

3.1.4 Age 18 years.

3.1.5 Life expectancy 3 months.

3.1.6 ECOG performance status 0-2 / Karnofsky 60% (see **Appendix B**).

3.1.7 No minimum period since last therapy is defined, but patients must have adequate organ function not toxicity as defined in 3.1.8, and preexisting non-hematological dysfunction <grade 2.

3.1.8 Patients must have normal organ and marrow function as defined below:

- absolute neutrophil count 1.5 x 109/l
- platelets 100 x 109/l
- total bilirubin < 2 x upper limit of normal
- AST (SGOT) / ALT (SGPT) 2.5 x upper limit of normal
- creatinine 1.5 x upper limit of normal

3.1.9 Patients with known brain metastases may be included in this study if they fulfill all of the following criteria:

- the lesions have remained radiologically stable for at least six weeks after completion whole brain irradiation, and remain stable at the time of study entry
- there is no mass effect present radiologically
- the patient is no longer receiving steroids to control symptoms of brain metastases

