**9.1.3 Target lesions**

All measurable lesions up to a maximum of five lesions per organ and 10 lesions in total representative of all involved organs should be identified as **target lesions** and recorded and measured at baseline. Target lesions should be selected on the basis of their size (lesions with the longest diameter) and their suitability for accurate repeated measurements (either by imaging techniques or clinically). A sum of the longest diameter (LD) for all target lesions will be calculated and reported as the baseline sum LD. The baseline sum LD will be used as reference by which to characterize the objective tumor response.

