**9.3** **Response Criteria**

**9.3.1 Evaluation of target lesions**

Complete Response (CR)

Disappearance of all target lesions

Partial Response (PR)

At least a 30% decrease in the sum of the longest diameter (LD) of target lesions, taking as reference the baseline sum LD

Progressive Disease (PD)

At least a 20% increase in the sum of the LD of target lesions, taking as reference the smallest sum LD recorded since the treatment started or the appearance of one or more new lesions

Stable Disease (SD)

Neither sufficient shrinkage to qualify for PR nor sufficient increase to qualify for PD, taking as reference the smallest sum LD since the treatment started

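### Section 9.1.1 accepts PET for sizing measurable lesions without any measurement rule, although the primary endpoint rests on longest diameter alone

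*Protocol*

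**What the plan says.** Protocol section 9.1.1 defines a measurable lesion by its longest diameter, with a 20 mm threshold "with conventional techniques (PET, CT, MRI, x-ray") and a 10 mm threshold on spiral CT. Two other sections depend on this definition:

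- **Eligibility.** Section 3.1.2 requires measurable disease and tells the reader "See section 9.1.1 for the evaluation of measurable disease".
- **Target lesions.** Section 9.1.3 takes as targets "All measurable lesions up to a maximum of five lesions per organ and 10 lesions in total", and their diameters make up the baseline sum.

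Section 9.1 states that "Changes in only the largest diameter (unidimensional measurement) of the tumor lesions are used in the RECIST criteria", and section 9.3.1 sets partial response at "At least a 30% decrease in the sum of the longest diameter (LD) of target lesions". Section 11 makes complete or partial response at the end of cycle 2 the primary endpoint.

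Section 9.1.1 goes on to give paragraphs on clinical lesions, chest x-ray, CT and MRI, ultrasound, endoscopy and laparoscopy, and cytology and histology. It gives none on PET. The ultrasound paragraph rules that technique out for measuring lesions when objective response is the primary endpoint, apart from a limited role as an alternative to clinical measurement of superficial lesions. Section 9.1.2 classes abdominal masses not followed by CT or MRI as non-measurable.

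In the section 2.2 summary of phase 1 experience, the study that used "repeat cycles of 1 week on/1 week off using b.i.d. dosing" reports: "Five patients (cervical, renal, sarcoma, melanoma, and colon) had stable disease". It adds: "The melanoma patient showed decreased 18[F]-fluorodeoxyglucose uptake on PET scan prior to progression of disease".

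**The concern.** PET images tracer uptake. The protocol's response criteria concern length. If a lesion is sized on PET, its apparent extent may depend on how strongly it takes up tracer as well as on its physical size. That dependence is general reasoning and is not stated in the protocol, but it is the reason a PET diameter needs a measurement rule before it can serve a diameter endpoint. Section 9.1.1 supplies none: no acquisition standard, no definition of the lesion edge and no uptake threshold.

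The omission is also at odds with the rest of the section. Ultrasound, an anatomical technique, is restricted because response is the primary endpoint, while a functional technique is admitted with no limit. Section 9.1.2 already treats CT or MRI follow-up as the condition for abdominal masses to be measurable, which does not fit with PET as a stand-alone sizing method there.

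At stake is the classification of a few patients. In each BRAF subgroup, one response among 13 patients continues accrual and five among 37 declare the drug active. There is no concurrent control arm in which the same misclassification would also appear.

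**Working it through.** **1. Does the text let a PET-sized lesion decide the endpoint?**

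- Section 9.1.1: PET is accepted for the 20 mm longest-diameter threshold.
- Section 3.1.2: eligibility refers to 9.1.1.
- Section 9.1.3: target lesions are drawn from measurable lesions.
- Section 9.3.1: partial response is a fall of at least 30% in the sum over target lesions. A single 20 mm target, for example, must read 20 × 0.7 = 14 mm or less.
- Section 11: that response is the primary endpoint.

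Each step is explicit, so the answer is yes. The partial exception is an abdominal mass not followed by CT or MRI (section 9.1.2).

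**2. What does the phase 1 case show?**

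There was one melanoma patient among 19 evaluable patients, treated one week on and one week off, whereas this trial doses continuously. The outcome was stable disease, with lower FDG uptake and later progression. No PET diameter is reported, and the patient was not counted as a responder. The case therefore shows that uptake fell without objective response. It does not show that PET sizing produced a false response.

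**3. Do the stated error rates reproduce?**

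Inputs from section 11: n1 = 13, stop at 0 responses; n = 37, so 24 more patients in stage 2; reject the drug at 4 or fewer responses; null rate 0.05, alternative 0.20.

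P(declare active) = Σ over x = 1 to 13 of P(X1 = x) × P(X2 ≥ 5 − x), with X1 ~ Bin(13, p) and X2 ~ Bin(24, p).

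At p = 0.05:

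| x | P(X1 = x) | P(X2 ≥ 5 − x) | product |
|---|---|---|---|
| 1 | 0.3512 | 0.0298 | 0.0105 |
| 2 | 0.1109 | 0.1159 | 0.0129 |
| 3 | 0.0214 | 0.3392 | 0.0073 |
| 4 | 0.0028 | 0.7080 | 0.0020 |
| ≥ 5 | | 1 | 0.0003 |

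The sum before rounding is 0.0329, matching the stated 3.3%. At p = 0.20 the same formula gives 0.8583, so the type II error is 0.1417, matching the stated 14.2%.

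**4. How much misclassification can the rule tolerate?**

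Assumption: a share f of true non-responders is misread as responders and nothing else changes. The documents give no value for f. The apparent response rate for an inactive drug is then p = 0.05 + 0.95f. The chance of passing stage 1 is 1 − (1 − p)^13.

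| f | p | pass stage 1 | declare inactive drug active |
|---|---|---|---|
| 0 | 0.0500 | 48.7% | 3.3% |
| 1% | 0.0595 | 55.0% | 6.1% |
| 2% | 0.0690 | 60.5% | 10.0% |
| 3% | 0.0785 | 65.5% | 14.9% |
| 5% | 0.0975 | 73.7% | 27.0% |

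The 5% target is crossed at f of about 0.65%, where p is 0.0562. These figures describe the design's tolerance to any cause of false responses. They do not estimate what PET would do.

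**The case against.** The strongest case against is that the protocol already has safeguards and that nothing in it demonstrates harm from PET.

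- **Selection of targets.** Section 9.1.1 requires accurate measurement, and section 9.1.3 asks for lesions suited to accurate repeated measurement. An investigator could fairly reject a lesion with an unstable PET edge. This stands, but it leaves to judgement what the technique list openly permits.
- **Same technique.** Section 9.2 asks for one technique at baseline and follow-up. PET at both times complies, so the rule does not help here.
- **Confirmation.** Section 9.4.1 requires a repeat assessment at least 4 weeks later. This would remove a transient change but not a sustained fall in uptake.
- **Independent review.** Section 9.6 has all responses reviewed with files and images, which is a real check. It takes place at the study's completion, after the 13-patient decision, and under criteria that accept PET.

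A reader might infer that the protocol's own phase 1 data show PET sizing creating false responses. They do not: the patient was classed as having stable disease, no diameter is reported, and the schedule differed. A reader might also infer that the bias can only favour the drug. That is not shown either, since by the same mechanism rising uptake could enlarge an apparent lesion and hide a true response or suggest progression. Nor can the larger false-positive figures in the table be attributed to PET. If PET sizing applied to 10% of patients, a cohort-wide false-response rate of 5% would need half of them to be misread (0.05 / 0.10). Nothing in the protocol makes that plausible.

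**Conclusion.** The point holds as a defect in a stated measurement rule. Section 9.1.1 admits PET to the sizing of measurable lesions, and so to eligibility and target lesions, with no measurement rule. This is in a trial whose primary endpoint is scored on longest diameter alone, under a section that restricts ultrasound for that very reason. The phase 1 case supports caution because it shows uptake falling on this drug without objective response, and it supports no more than that.

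The size and direction of any bias are unknown. The documents say neither how often sites would size on PET nor how often such sizing would misclassify a patient. The only quantitative statement available is conditional: if about 1% of true non-responders were misread as responders, the false-positive rate in a subgroup would be about 6.1% against the stated 3.3% and the 5% target. If PET is never used for sizing, the stated 3.3% is unaffected from this source. Existing safeguards reduce the risk but do not close it. The change is worth making because the margin is narrow and the correction costs almost nothing.

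**What to change.** Delete PET from the parenthesis in section 9.1.1; section 3.1.2 then follows through its cross-reference. Add one sentence saying that a PET finding may prompt a CT or MRI but that a PET measurement does not enter the sum of longest diameters. Leave the existing rules for CT, MRI, x-ray and clinical lesions as they are, and keep the limited ultrasound alternative for superficial nodes, subcutaneous lesions and thyroid nodules. A replacement sentence that listed the only permitted techniques could remove that ultrasound option by accident, so the deletion is the safer edit.

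The cost is a small wording change. The downside is that a lesion seen only on PET must be sized on CT or MRI before it counts as measurable. A patient whose only qualifying lesion was sized on PET would need that measurement before entry.
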